#### Model Fidelity

The *Independent Housing and Support for people with mental disorders – Fidelity Scale* [Selbstbestimmtes Wohnen mit Unterstützung für Menschen mit psychischen Beeinträchtigungen – Modelltreue Skala (SeWo-Psych)] [68] will be used to assess model fidelity of IHS and to compare process quality of IHS and RCS/TAU programmes. This scale will be conducted as an interview with heads of the residential rehabilitation services (IHS and RCS/TAU) at the start of the recruitment phase at the respective service and one year after the last participant of the study has been recruited. The 32 items ask for the extent of agreement on the subscales 1) housing conditions, 2) team, 3) support conditions, and 4) orientation to inclusion in a 5-point Likert scale format. The scale has satisfactory psychometric properties. The SeWo-Psych refers to the *Quality Indicator for Rehabilitative Care* (QuIRC) [69] and is currently being validated in Germany.

The *Housing First Fidelity Scale* [70] will also be elevated. Housing First (HF) is a residential rehabilitation programme for homeless people in the United States and Canada [17]. The scale will be assessed at the same time points as the SeWo-Psych and will be utilised to enhance the comparability of IHS in Switzerland with the IHS of the Housing First program in North America. The 38-item interview asks heads of the residential rehabilitation settings to rate on a 5-point Likert scale the aspects of the subdimensions 1) housing choice and structure, 2) separation of housing and clinical services, 3) service philosophy, 4) service array, and 5) programme structure. Possible score range from 38 to 152 with higher score indicating higher fidelity with the HF program. The scale has shown promising utility, reliability, and validity [70].

## Data analyses

Relevant packages of the statistical software R will be used for conducting all statistical analyses [71]. For analysing and reporting, we follow the CONSORT guidelines for the reporting of non-inferiority and equivalence randomised trials [72, 73]. The main analyses will be performed using an a priori statistical analysis plan. For all analyses, Bonferroni corrections will be applied where necessary.

Missing data is expected due to refused items, missed appointments and drop-outs. With regard to recommended sensitivity analyses of missing data, we state the following assumptions about missing data: Missing data due to refused items is assumed to be independent of the respective treatment condition and to be completely related to the items refused. Thus, they are assumed to be missing at random (MAR). Due to the preference probably inherent in the investigated interventions and the associated difficulties [32, 37], missing data due to dropouts has to be assumed to be missing not at random (MNAR). Missing data will be analysed and imputation methods applied if appropriate [74, 75].

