### Sample size

The appropriate sample size is determined by the non-inferiority approach and was calculated for the primary outcome measure ‘Social Functioning Scale’ [46, 47]. This scale has been used in a subsample of a randomised Housing First trial, from where the necessary data has been taken [48]. For calculating the appropriate sample size of the RCT study site, the application ‘Power and Sample Size’ [49] was used applying the following parameters: Power: 0.9; significance level: 0.025; non-inferiority margin: 15; difference between treatments (group means): 111.2–106.7; standard deviation: 12; and allocation ratio: 1:1. This procedure yielded a sample size of 28 people to be included in each arm.

The OSD sample size is based on the calculation for the RCT. Thus, 28 participants will be included in the treatment arm. For propensity scoring, the many-to-one matching method was chosen. Here, it is recommended to have a 2–3 times larger control group to facilitate matching [50, 51]. Accordingly, 56 to 84 participants will be included in the control group.

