### Primary objective: care-related goal

For analysing the primary outcome variable social inclusion we will check for non-inferiority both in per-protocol and in imputed ITT samples to assess the security of inference of non-inferiority as recommended in the CONSORT guidelines for non-inferiority trials [72, 73].

Primary analysis will compare primary and secondary outcomes between IHS and RCS/TAU after 6, 12 and 24 months separately for both study sites. A repeated measure approach will be used where indicated. Non-inferiority of IHS compared to RCS/TAU will be accepted based on a 2.5% significance level if the lower bound of the 97.5% CI of M_IHS_-M_RCT/TAU_ is > δ = − 15, and vice versa, non-inferiority of IHS compared to RCS/TAU cannot be accepted if the lower bound of the 97.5% CI of M_IHS_-M_RCT/TAU_ is ≤ δ = − 15. This non-inferiority margin corresponds to one standard deviation of 15 scale scores (*m* = 100; *SD* = 15) on the primary outcome variable SFS [46, 47] and was chosen based on the clinical judgment of experts as no RCT investigating the SFS as outcome measure in a comparable sample was available [81]. In addition, assay sensitivity will be analysed by investigating pre-post differences in a first step. Assay sensitivity will be assumed, if there is a statistically and clinically significant pre-post increase in the SFS total scale score [82].

All other outcome measures will also be tested on their non-inferiority using the definition of margin δ as one standard deviation of the respective scale. Analyses will be extended to superiority testing in case of confirmed non-inferiority, and to interaction terms to explore mechanisms of treatment effects.

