### Limitations

There are some limitations possibly compounding the interpretation of the findings. Firstly, most of the measures were assessed based on self-reported answers of participants, which can differ from more objective views. Therefore, the key workers ratings of participants’ functioning will be also assessed. Where necessary, key workers will be supported in doing the ratings by study collaborators. Secondly, blinding of participants or study collaborators is not possible due to the housing nature of the investigated conditions. Thirdly, the current study proposes a pragmatic non-inferiority hypothesis because there was no former study investigating our primary outcome variable *Social Functioning Scale* (SFS) [46, 47] in a comparable service field. Therefore, a historical justification of the non-inferiority margin δ and of an assay sensitivity as is usually recommended in non-inferiority trials [72, 73] was not applicable. Nevertheless, proposing a superiority hypothesis would not be appropriate for the present research because of the mixed results in comparative effectiveness research regarding residential rehabilitation in non-homeless people with SMI [16, 19–22]. Furthermore, the sample size calculation is based on the primary outcome measure, therefore, the present study has possibly not included enough participants to detect statistical significant differences in secondary outcomes tested on superiority of IHS. Accordingly, analyses on secondary outcomes have to be interpreted in an exploratory manner. It is important to recognise that the failure to find a difference does not imply non-inferiority regarding the respective outcome variable [83]. And last but not least, the study is conducted as a field study in two separate service areas. Therefore, the generalisability to other regions or other service providers may be limited.

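### Bonferroni is fixed as the multiplicity correction where Holm's step-down procedure would give the same familywise error control and never reject less

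*Protocol article*

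**What the plan says.** The opening paragraph of Data analyses names one multiplicity method: "For all analyses, Bonferroni corrections will be applied where necessary". It refers the main analyses to a statistical analysis plan, which is not shown. No family of tests is defined in the article.

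Primary objective: care-related goal sets out the tests. Primary and secondary outcomes are compared at 6, 12 and 24 months, separately at each site. For the SFS, the lower confidence bound is compared with −15 at a 2.5% level that is not divided. For the rest: "All other outcome measures will also be tested on their non-inferiority using the definition of margin", with one scale SD as the margin. Superiority tests follow where non-inferiority is confirmed.

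Sample size gives the randomised site's planning inputs: "Power: 0.9; significance level: 0.025; non-inferiority margin: 15", "difference between treatments (group means): 111.2–106.7" and "standard deviation: 12; and allocation ratio: 1:1". The result is stated as: "This procedure yielded a sample size of 28 people to be included in each arm".

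On power beyond the SFS, Limitations says that "the present study has possibly not included enough participants to detect statistical significant differences in secondary outcomes tested on superiority of IHS" and treats the secondary analyses as exploratory.

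**The concern.** The article leaves open when a correction is needed, but not which one is used. Single-step Bonferroni tests each of m hypotheses at α/m. Holm tests the smallest p-value at α/m, the next at α/(m−1), and so on up to α, stopping at the first failure. Both hold the familywise error at α with no assumption about how the tests are correlated. Since no Holm threshold is below α/m, Holm keeps every Bonferroni rejection and can add more.

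So in any corrected family Bonferroni gives up some power and gains no error control in return. The plan runs many parallel tests on arms of 28. If several true effects lie in the same direction, as they would if IHS (Independent Housing and Support) is no worse on most scales, the later Holm steps are reached often and the difference becomes visible. At stake is failing to declare non-inferiority on secondary outcomes where it is true.

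**Working it through.** **Step 1: reproduce the planned sample size.** The inputs are all from Sample size: margin 15, difference 111.2 − 106.7 = 4.5 (it must be entered against IHS to reproduce the result), SD 12, α = 0.025 one-sided, power 0.90, allocation 1:1.

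n per arm = 2 × 12² × (1.960 + 1.282)² / (15 − 4.5)² = 27.4, rounded up to 28. This matches. At n = 28 the standard error is 12 × √(2/28) = 3.207, the non-centrality is 10.5/3.207 = 3.274, and power is Φ(3.274 − 1.960) = 0.906. The figure uses the whole 2.5% for one test.

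**Step 2: assumptions for the comparison.** Not in the article, and so assumed:
- Family size of seven or ten. Seven scored scales can be counted in the outcome section: HoNOS, m-GAF, SCL-K-9, MANSA, ESSI-D, CANSAS and OxCAP-MH. Counting met and unmet needs separately makes eight, so ten is a generous upper figure.
- The same true effect on every outcome in the family.
- Equicorrelated normal test statistics.
- A one-sided family level of 0.025.

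Each setting used 400,000 simulated sets. Non-centrality for an effect of d SD is d/√(2/28) = 3.742 × d.

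**Step 3: secondary non-inferiority, margin 1 SD, true difference 0 (non-centrality 3.742).**
- Uncorrected: Φ(3.742 − 1.960) = 96.3%.
- Seven outcomes, Bonferroni: Φ(3.742 − 2.690) = 85.3%. Holm: about 92–94% for correlations 0.2 to 0.6 (92.8% at 0.5).
- Ten outcomes, Bonferroni: Φ(3.742 − 2.807) = 82.5%. Holm: 91–93% for correlations 0.2 to 0.6.
- All declared: seven outcomes at correlation 0.5, 55% against 82%; ten outcomes, 27–48% against 70–80%.

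**Step 4: secondary superiority, power per test, Bonferroni against Holm.**
- Seven outcomes, correlation 0.5: 2.6% against 3.0% at 0.2 SD; 5.9% against 7.0% at 0.3 SD; 20.7% against 25.4% at 0.5 SD; 62.0% against 72.8% at 0.8 SD.
- Ten outcomes, correlation 0.4: 2.0% against 2.2%, 4.6% against 5.2%, and 17% against 21% at 0.2, 0.3 and 0.5 SD.
- If only three of seven outcomes have a true effect of 0.5 SD (correlation 0.5): 20.6% against 21.6%.
- The chance of at least one rejection is identical, because both methods apply α/m to the smallest p-value.
- For scale, the uncorrected power at 0.5 SD is 46%. Most of the loss there comes from correcting at all.

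**Step 5: SFS, only if the three visits are taken as one corrected family and the design assumptions hold at each.** Bonferroni: Φ(3.274 − 2.394) = 81% per visit. Holm: 87–88% for correlations 0.2 to 0.6. All three visits at correlation 0.5: 63% against 78%.

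**Step 6: error control.** With no true effects the familywise error was the same under both methods (0.013 to 0.025). With three of seven effects true it was 0.018 for Holm and 0.013 for Bonferroni, both within 0.025. Holm lost no Bonferroni rejection.

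**The case against.** The strongest reply is that nothing here is wrong. Bonferroni is valid and conservative, it applies only where a correction is needed, and the families belong in an analysis plan that is not shown. That stands: the point is about efficiency. It does not remove the point, because the article has already chosen the method.

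Second, the plan decides non-inferiority by a confidence bound, and Bonferroni supplies simple simultaneous bounds that fit such a rule. Holm does not do so directly. This also stands, and it is the real cost of the change. It is manageable if the stepped bounds themselves are compared with the margin.

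Third, the gain depends on the setting. It is small for superiority at modest effects, and the article itself describes earlier differences between the housing types as small or absent. It is also smaller at the observational site: with 28 against 56–84 and ignoring matching, the ten-outcome non-inferiority scenario gives 93.5–96.2% with Bonferroni and 98–99% with Holm.

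A reader might also infer that the study admits to being short of power. The documents do not support that. Limitations speaks of a possible shortage, only for superiority tests of secondary outcomes, which it labels exploratory. The SFS is planned at 90%.

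**Conclusion.** The point holds as a minor, inexpensive improvement. In any family of two or more corrected tests, Bonferroni gives up power that Holm would keep at the same error rate. Under the assumptions in the working, the gain at 28 per arm is about 7 to 11 points per outcome for secondary non-inferiority. For superiority at 0.5 SD or less it is at most about 5 points, and for the chance of any finding it is nil. These sizes rest on assumed family sizes, correlations and equal effects; the ordering of the two methods does not.

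It would be tempting to conclude that the primary analysis loses power. That is not established: both the sample size and the SFS decision rule use 2.5% undivided, so a loss arises only if the three visits are treated as one corrected family. Nor does the article say that the per-protocol and intention-to-treat analyses are corrected as a pair, so nothing needs changing there.

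**What to change.** Replace the Bonferroni sentence in Data analyses with wording such as:

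> Where a family of tests needs correction, the Holm step-down procedure is used. For confidence-bound decisions the one-sided bounds are taken at levels 1−α/m, 1−α/(m−1), and so on, in order of the p-values, and these stepped bounds are the ones compared with the margin.

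Label any unadjusted intervals as descriptive and do not use them for the decision. Otherwise an unadjusted bound could lie above the margin while the Holm decision withholds non-inferiority.

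The cost is this sentence, one option in R (`p.adjust`, method `holm`), which the plan already uses, and a matching line beside the confidence-bound rule wherever a corrected family is decided that way. The planned 28 per arm does not change. The downside is that Holm does not give simple simultaneous intervals at one common level.

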### Baseline characteristics

In the RCT sample, equivalence of baseline characteristics of the two study conditions IHS and RCS/TAU will be assessed descriptively as differences could have only occurred by chance.

To adjust for potential selection bias in the OSD sample, propensity score (PS) matching will be conducted. PS matching is a statistical method in which one case in the investigational condition is matched with one or more control cases based on the PS of each one, while the PS is the statistical probability of each case to receive the investigational condition based on relevant covariates [76, 77].

Relevant covariates for the PS model, meaning those covariates causally related to treatment condition and to the primary outcome of social inclusion, will be selected according to theoretical assumptions and empirical findings [78]. The propensity scores will be obtained by logistic regression [76, 79].

As matching method, many-to-one matching (m:1) with nearest neighbour approach (without replacement) will be applied [80]. In this method, every IHS participant will be matched with a variable amount between one to three participants of the RCS condition. This method is expected to generate the best matching quality with the lowest risk of bias [50, 51, 75]. Covariate balance will be checked before and after matching by recommended balance checks [50, 51, 77].

### Primary objective: care-related goal

For analysing the primary outcome variable social inclusion we will check for non-inferiority both in per-protocol and in imputed ITT samples to assess the security of inference of non-inferiority as recommended in the CONSORT guidelines for non-inferiority trials [72, 73].

Primary analysis will compare primary and secondary outcomes between IHS and RCS/TAU after 6, 12 and 24 months separately for both study sites. A repeated measure approach will be used where indicated. Non-inferiority of IHS compared to RCS/TAU will be accepted based on a 2.5% significance level if the lower bound of the 97.5% CI of M_IHS_-M_RCT/TAU_ is > δ = − 15, and vice versa, non-inferiority of IHS compared to RCS/TAU cannot be accepted if the lower bound of the 97.5% CI of M_IHS_-M_RCT/TAU_ is ≤ δ = − 15. This non-inferiority margin corresponds to one standard deviation of 15 scale scores (*m* = 100; *SD* = 15) on the primary outcome variable SFS [46, 47] and was chosen based on the clinical judgment of experts as no RCT investigating the SFS as outcome measure in a comparable sample was available [81]. In addition, assay sensitivity will be analysed by investigating pre-post differences in a first step. Assay sensitivity will be assumed, if there is a statistically and clinically significant pre-post increase in the SFS total scale score [82].

All other outcome measures will also be tested on their non-inferiority using the definition of margin δ as one standard deviation of the respective scale. Analyses will be extended to superiority testing in case of confirmed non-inferiority, and to interaction terms to explore mechanisms of treatment effects.

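### One fixed 2.5% non-inferiority rule covers the SFS at three visits, with no primary visit or success rule, while the RCT is sized for a single test

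*Protocol article*

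**What the plan says.** All references are to the protocol article.

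- **Sample size.** The RCT calculation uses "Power: 0.9; significance level: 0.025; non-inferiority margin: 15", "difference between treatments (group means): 111.2–106.7" and "standard deviation: 12" with 1:1 allocation, and arrives at 28 per arm. This is one comparison of SFS means, and no visit is attached to it.
- **Primary objective: care-related goal.** "Primary analysis will compare primary and secondary outcomes between IHS and RCS/TAU after 6, 12 and 24 months separately for both study sites". Non-inferiority is accepted at a 2.5% level when the lower bound of a 97.5% confidence interval for the mean difference lies above −15. On the model, the text adds: "A repeated measure approach will be used where indicated".
- **Data analyses.** "For all analyses, Bonferroni corrections will be applied where necessary". The number of tests to be corrected for is not given. A separate a priori analysis plan is announced.
- **Study design** gives the RCT part and the observational (OSD) part each its own non-inferiority aim. **Secondary objective** allows the analyses to be repeated on pooled data if the two parts look homogeneous.

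No section names a primary visit or says which of the three visits must meet the margin for the claim to be made.

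**The concern.** The sample size and the decision rule describe different experiments. The first is a single test. The second is the same 2.5% test made three times within each site, with nothing said about how the three results combine. The Bonferroni sentence does not settle this: any correction across visits changes the 2.5% level that the acceptance rule fixes, and no correction leaves the family of tests open.

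At stake is what a positive result would mean. The trial is open, and without a stated rule non-inferiority could be reported from whichever visit passes. A stricter rule adopted later would leave the RCT with less power than it states.

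**Working it through.** **Inputs.** From Sample size: margin 15, SD 12, assumed difference 111.2 − 106.7 = 4.5, one-sided level 0.025, power 0.90, 28 per arm. Not in the documents and therefore assumed: an equal correlation ρ between the visit-specific test statistics, shown for 0.4 to 0.8, and the same true difference and SD at every visit.

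**Step 1: the stated size.** n = 2 × [12 × (1.960 + 1.282) / (15 − 4.5)]² = 27.45, so 28 per arm. The figure reproduces if the 4.5 points are taken as a disadvantage of IHS and 0.025 as one-sided. SE = 12 × √(2/28) = 3.207, and 10.5 / 3.207 = 3.274. Power = Φ(3.274 − 1.960) = 90.6% (89.5% by noncentral t). With one named test, the stated design holds.

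**Step 2: any visit may pass, uncorrected.** At a true difference of −15, the error per site is P(at least one of three Z > 1.960), with Z trivariate normal.

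| ρ | Error per site | Chance that at least one visit passes (RCT, design difference) |
|---|---|---|
| 0.4 | 6.6% | 99.0% |
| 0.6 | 5.9% | 98.0% |
| 0.8 | 4.9% | 96.2% |

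The error is two to two and a half times the stated 2.5%. Power is above 90%.

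**Step 3: Bonferroni over three visits.** The level is 0.025 / 3 = 0.00833, with critical value 2.394. Per-test power = Φ(3.274 − 2.394) = 81.1% (78.6% by t). For 90% per test, n = 2 × [12 × (2.394 + 1.282) / 10.5]² ≈ 35.3, so 36 per arm. The error is held. The chance that at least one visit passes is 90.6% (ρ = 0.8) to 96.5% (ρ = 0.4), but that is power for a claim about an unspecified visit, not for the comparison that was sized.

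**Step 4: all three visits must pass at 2.5% each.** The error stays at or below 2.5%. RCT power is P(all three Z > 1.960 with mean 3.274): 78.0%, 80.5% and 83.6% for ρ = 0.4, 0.6 and 0.8 (normal approximation).

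**Step 5: the interval.** A one-sided 97.5% bound tests at 2.5% and matches Step 1. The lower end of a two-sided 97.5% interval tests at 1.25%: power Φ(3.274 − 2.241) = 84.9% (83.0% by t), and 33 per arm would be needed.

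**Step 6: baseline SFS as a covariate (optional gain).** The residual SD is 12 × √(1 − r²), where r is the baseline to follow-up correlation. The documents do not give r, so these values are assumed.

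| r | SD | Power at 28 per arm, one test at 0.025 (t to normal) |
|---|---|---|
| 0.3 | 11.45 | 92.1% to 93.0% |
| 0.5 | 10.39 | 96.0% to 96.6% |
| 0.7 | 8.57 | 99.4% to 99.6% |

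**The case against.** The strongest defence is that this is a journal article that points to an a priori analysis plan, promises multiplicity correction and foresees a repeated-measures model. The primary visit and the covariates may well be settled in that plan. For covariates this stands. For the visits it does not fully answer the point, because the article itself fixes the 2.5% rule, lists the three visits as the primary analysis and sizes one test. These statements do not fit together as written.

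Four stronger readings are tempting, and the document does not support them.

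- **A reader might infer that both the 2.5% error and the 90% power are lost.** They do not fail together. Under the any-visit rule the error rises and so does power. Under Bonferroni or the all-visits rule the error holds and the relevant power falls. With one named visit both hold.
- **A reader might infer that the means are unadjusted and that this is an error.** The article gives only a difference in means. It leaves room for a repeated-measures model, and the OSD is propensity-score matched. Even an unadjusted difference would be valid in the RCT, only less precise.
- **A reader might count both sites as one family.** That gives 1 − (1 − 0.049)² to 1 − (1 − 0.066)², about 10% to 13%. But the sites are analysed separately, each with its own aim, and no rule says that a pass at either site suffices. The firm figure is the one within a site.
- **A reader might take the 97.5% interval as two-sided.** The stated 2.5% level and the 28 per arm both point to a one-sided bound. The wording needs clarifying, but there is no demonstrated loss of power.

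**Conclusion.** The point holds in limited form. The article applies one fixed 2.5% rule to three SFS visits per site without a primary visit or a success rule, and this agrees neither with a sample size for one test nor with a conditional Bonferroni correction. No multi-visit reading examined delivers both a 2.5% error per site and 90% power for the comparison that was sized. The cost is an error of about 5% to 6.6% per site, or per-test power of 79% to 81%, or all-visit power of about 78% to 84%, depending on the rule left unstated. The first and third ranges rest on an assumed between-visit correlation of 0.4 to 0.8, and all the power figures rest on the design values (difference 4.5 against IHS, SD 12, 28 per arm with complete data). The defect lies in how the rule is specified. The sample size calculation itself is sound for a single test.

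**What to change.** 1. Pre-specify one SFS test in the RCT as primary, at one-sided 2.5%: either one visit (24 months, for example; the documents do not dictate the choice) or one repeated-measures contrast.
2. Make the other visits supportive, or test them in a stated fixed order so that the first test keeps the full 2.5%. State that Bonferroni does not apply to the primary test.
3. State the role of the OSD and of the pooled analysis. If either keeps a non-inferiority claim, give it its own single pre-named test.
4. State that the bound is the one-sided 97.5% limit, that is, the lower limit of a two-sided 95% interval.
5. As a free improvement rather than the correction of an error, include baseline SFS as a covariate in the RCT model. This should not be carried over to the OSD without thought, since consent there is sought only after admission to the setting.

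The cost is wording in the protocol and analysis plan, settled before outcomes are compared by arm. No new data or participants are needed, and the stated 2.5% and 90% are restored for the named test. If the analysis plan already names that test, the protocol only needs to be aligned with it. The downside is that a pass at another visit alone can no longer be headlined.
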